##### Determinants of EENC performance amongst health workers

Determinants of EENC performance by health workers will be quantified by using a structured questionnaire (Additional file 2) that was developed based on the Theory of Planned Behaviour. [27–30] The questionnaire will measure determinants of behaviour: attitude, subjective norms, perceived behaviour controls and behaviour intentions that would influence future behaviour. The higher the total score of the determinants, the higher the likelihood of staff practising EENC in their daily work. Data will be collected six times from both groups during the study period: 1) before EENC coaching, 2) immediately after randomisation, 3) three months after randomisation, 4) six months after randomisation, 5) nine months after randomisation, and 6) one year after randomisation. Provincial officials will remind by telephone each district to fill out their own questionnaire every three months. Administered questionnaires will be saved in each district until provincial supervisors or assessors visit the district, at which point they will collect the questionnaires and submit them to the investigators. In the intervention group, checklists used for the self-managed continuous monitoring and interviews with pregnant women who receive the EENC will be stored and compared with the results of the questionnaire.

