### Recruitment and allocation

#### Recruitment

After identifying eligible participants, written informed consent will be obtained from each. To obtain sufficient numbers of participants from each district hospital and to minimise loss to follow up, we will involve all district hospital directors. Directors will usually monitor, supervise and encourage their staff in their duties. Getting directors’ participation is therefore critical. Researchers, together with provincial and district staff, will set up a schedule to ensure that all participants are in the district hospital at the time of data collection or supervision. In the intervention group, central and provincial staff will also remind district directors and local staff to conduct self-managed continuous monitoring and submit reports. The expected enrolment period is July 20th, 2017 to July 20th, 2018.

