#### Blinding

Blinding of participants would be difficult in this study due to the nature of the intervention. We will choose assessors amongst central and provincial officials who do not know about the allocation. Standardised checklists will be used for outcome measurement to minimise bias. Team members who manage data will be blinded until the code is open. Members who analyse data will also be kept blinded.

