##### Control group: Supervisory visit

After randomisation, supervision will be provided every three months to the control group. Members of the Provincial Health Department and/or the Provincial Hospital will visit district hospitals to observe whether district health workers are providing appropriate care through direct observation and/or chart review and whether there are sufficient essential medicines and equipment available using standardised checklists. Provincial supervisors will also interview mothers who gave birth at a hospital to determine whether they have received appropriate care. Provincial supervisors will give feedback to district health workers as needed and ask them to solve any problems that are detected.

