**Fig. 2 Fig2:**
[figure not shown]
Trial schedule

District hospitals that have not yet received EENC coaching will receive coaching before randomisation. Pre-coaching evaluation will be done to measure determinants of EENC performance and knowledge related to neonatal care before the introduction of EENC.

After the coaching, the districts will be randomly allocated into two groups. A research team member will distribute and explain a structured questionnaire to be filled out by the district participants to measure determinants of EENC performance and will administer written and simulation tests to measure EENC knowledge and skills. The collected data will be used as baseline data.

District hospitals that are allocated into the intervention group will receive a half day of on-the-job training on self-managed continuous monitoring. A research staff member will explain the concept, schedule, procedure and checklists of self-managed continuous monitoring.

After randomisation, district hospitals in the intervention group will conduct self-managed continuous monitoring and submit quarterly reports to the province. In the control group, provincial supervisors who are not involved in the research will visit districts every three months to supervise implementation of EENC and give feedback to district health workers.

Study participants will be monitored until one year after entry into this study or withdrawal from the study for any reason. The date of the final evaluation will be determined once a schedule for enrolment is set for each district. We will allow a variation of a month around the endpoint for timing of the final evaluation. The outcome data on participants who withdraw from the study before one year will be collected at the time of withdrawal.

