##### Skills for EENC amongst health workers

Data will be collected twice in both groups during the study period: 1) immediately after randomisation and 2) one year after randomisation. We will use simulation tests to quantify the level of skills for EENC (Additional file 4). The data will be collected when provincial officials visit the districts.

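### Supervisors who visit only control hospitals may collect the primary-outcome questionnaires, so the collection route differs by arm; assessor blinding for skills and the hospital checklist is not secured

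*Protocol article*

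**What the plan says.** The primary endpoint is the change from baseline to one year in a questionnaire score that participants fill in themselves (Data analysis; Participant timeline). The form is completed six times. Five of these fall after randomisation: immediately, and at 3, 6, 9 and 12 months.

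On handling the forms, the section on determinants of EENC performance states: "Administered questionnaires will be saved in each district until provincial supervisors or assessors visit the district, at which point they will collect the questionnaires". The collectors then pass them to the investigators.

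On supervision, the control-group section states: "After randomisation, supervision will be provided every three months to the control group". It adds: "Members of the Provincial Health Department and/or the Provincial Hospital will visit district hospitals". The visitors look at care or charts, check supplies, interview mothers and ask staff to put problems right. The Participant timeline says of the same arm that "provincial supervisors who are not involved in the research will visit districts every three months". Of the other arm it says that "district hospitals in the intervention group will conduct self-managed continuous monitoring and submit quarterly reports to the province". No supervisory visit is described there.

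On blinding, participants are not blinded. For assessors the Blinding section says: "We will choose assessors amongst central and provincial officials who do not know about the allocation". The Recruitment section says: "In the intervention group, central and provincial staff will also remind district directors and local staff to conduct self-managed continuous monitoring and submit reports". The section on skills says: "The data will be collected when provincial officials visit the districts". Provincial officials also complete the hospital environment checklist.

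**The concern.** There are two separate issues.

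The first concerns the primary outcome. If supervisors may collect the completed forms, and supervisors go only to control hospitals, then control staff can be asked to give self-reported answers on attitude, norms, perceived control and intention to the people who review their practice. Intervention staff give theirs to an assessor. Who will handle a form can influence how it is answered, and here that depends on allocation. No analysis described in the article could separate such an effect from the effect of the intervention. The same sentence also contradicts the statement that these supervisors are outside the research.

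The second concerns outcomes recorded by an observer: the simulation skills test and the hospital checklist. Assessors are to be unaware of allocation, yet they are drawn from the levels of administration that carry out activities specific to one arm. If the same people held both roles, their ratings would not be blinded.

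**Working it through.** The article gives no figure on this point, so the check sets its statements side by side.

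**Supervisors' role.** The Participant timeline places the supervisors outside the research. The section on determinants has them collect primary-outcome forms and submit them to the investigators. Collecting and forwarding primary-endpoint data is a research task, so both statements cannot hold.

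**Collection opportunities by arm.** Supervisory visits every three months over one year fall nominally at 3, 6, 9 and 12 months.
- Control: 12 / 3 = 4 possible collections by a supervisor.
- Intervention: 0, because no supervisory visit is described. These forms wait for an assessor.

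**Which forms are exposed.**
- The form used as baseline is handed out and explained by a research team member (Participant timeline), so the supervisor route bears little on it.
- The forms at 3, 6 and 9 months coincide with control supervision and are the most exposed.
- The one-year score belongs to a scheduled final evaluation, which makes assessor collection likely. However, the collection sentence follows a list of all six time points and exempts none of them.

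**Route into the primary analysis.** The contrast is baseline to one year, so the interim scores are not part of it directly. Missing one-year scores are filled by last observation carried forward, which can put a 3-, 6- or 9-month score in the place of the one-year score. Multiple imputation by chained equations may also draw on interim scores; the article does not say whether it will.

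**Assessor pool against staff active in one arm.**
- Assessors: central and provincial officials unaware of allocation (Blinding).
- Monitoring reminders to the intervention arm: central and provincial staff (Recruitment), provincial officials (intervention-group section).
- Quarterly reports from the intervention arm: sent to the province (Participant timeline).
- Supervision of the control arm: Provincial Health Department and/or Provincial Hospital (control-group section).

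The levels of administration overlap. Whether the individuals overlap is not stated either way, and no sentence requires the roles to be held by different people.

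**Outcomes touched by the second issue.** Both skills measurements, immediately after randomisation and at one year, are taken when allocation already exists. The hospital checklist is completed before randomisation and at one year, so only its second reading is exposed. Knowledge is a written test and leaves less to the observer. The primary outcome is completed by unblinded participants, so assessor blinding gives it little protection in any case.

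**The case against.** The strongest reply has four parts.

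First, a reader might infer that the stated assessor blinding is not achieved. The article does not support this. The Blinding section limits assessors to officials who are unaware of allocation, and a shared institution does not show shared individuals. With 6 and 9 hospitals per province it is plausible that a province's own officials would learn the arms, but that is a prediction. The objection stands: the text supports not secured, and no more.

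Second, a reader might infer that social desirability acts in the control arm alone. This is not established. Forms are stored in the district in both arms, and directors who supervise staff are involved at all hospitals. Intervention staff are evaluated by peers, and their monitoring checklists are compared with the questionnaire results. Pressure to answer favourably may exist in both arms. What differs by arm on the face of the text is the collector.

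Third, the supervisor route concerns mainly interim forms. This also stands, and it reduces the reach of the point. It does not remove it, because of the carry-forward rule and because the one-year form is not exempted.

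Fourth, handling of forms is operational detail that an article may leave to the full protocol. That would answer a complaint about silence on envelopes. It does not answer a sentence that names supervisors as collectors and conflicts with another sentence.

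**Conclusion.** The point holds in limited form. The article contradicts itself on whether supervisors take part in the research. As written, it also allows a collection route for the primary-outcome form that depends on arm: up to four supervisor collections in control hospitals and none in intervention hospitals. This assumes that supervision runs to its stated schedule and that intervention hospitals receive no supervisory visit, as described.

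The effect on the result cannot be estimated from the article. It is tempting to say that each point of inflation in control scores would take one point off the 5-point difference sought. That is arithmetic on a hypothetical bias at one year and says nothing about its likely size. Since intervention staff may also feel pressure to answer well, the direction is unknown too.

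For the simulation skills test and the one-year hospital checklist, blinding is promised but not secured, because nothing separates assessors from supervisors or from staff who send monitoring reminders. Failure of blinding is not shown. The correction should still be made, because the risk is easy to prevent before data collection and cannot be repaired by analysis afterwards.

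**What to change.** Three changes of wording and procedure:

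1. In the section on determinants of EENC performance, remove supervisors as collectors, so that it agrees with the Participant timeline.
2. Use one procedure in both arms and at every time point: participants seal their own form, assessors collect it, and only the research team opens it.
3. In the Blinding section, state that nobody who supervises control hospitals or sends monitoring reminders to intervention hospitals acts as an assessor. The telephone reminders to complete the questionnaire go to both arms and need not be covered.

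Exchanging assessors between the two provinces is not needed for this. It would add travel, and the Study setting section already notes differing road conditions and remote villages.

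The cost is small: envelopes, a longer wait before control forms are collected (as intervention forms already have), and a slight restriction on who can be assigned as an assessor. Design, sample size and analysis are unchanged.

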##### Knowledge of EENC amongst health workers

Data will be collected three times in both groups during the study period: 1) before EENC coaching, 2) immediately after randomisation, and 3) one year after randomisation. We will use written tests to quantify the level of knowledge of EENC (Additional file 3). The data will be collected when provincial officials visit the districts.

##### Skills for EENC amongst health workers

Data will be collected twice in both groups during the study period: 1) immediately after randomisation and 2) one year after randomisation. We will use simulation tests to quantify the level of skills for EENC (Additional file 4). The data will be collected when provincial officials visit the districts.

##### Hospital environmental changes facilitating implementation of EENC

The data will be collected twice in both groups during the study period: 1) before randomisation and 2) one year after randomisation by the provincial officials. We will use a checklist designed by the Lao MoH and the WHO to quantify the district hospital’s level of commitment and the availability of essential equipment, commodities, medications and human resources in each facility (Additional file 5).

We will also compare the cost spent for maintenance activities between the intervention and control groups.

##### Potential confounders

We will collect participants’ demographic data such as age, sex, ethnicity, title, position and professional experience at baseline. A self-administered questionnaire will be used (Additional file 6). Data on those who discontinue participation will be collected at the time of dropping out.

#### Data management

Collected paper data will be handed to the collaborating organisation and stored in the WHO Lao County Office. All documents will then be moved to the office at Teikyo University Graduate School of Public Health for data entry and coding. Double data entry will be conducted to minimise error. Personal information will be anonymised by allocating an identification number for each participant. A list of identification numbers is available when a participant must be identified. We will keep both paper and electronic data in the research office of the Teikyo University Graduate School of Public Health in a secure manner. Data will be kept at least five years after study completion, then discarded. Anonymised data could be shared with collaborating organizations such as the Lao MoH and the WHO.

#### Data analysis

To ensure that cluster randomisation is successful, the significance of differences between the intervention and control groups for the baseline characteristics of participants such as age, sex, position, experience in years will be examined using the chi-squared test and *t*-test.

The primary endpoint is the change in determinants of EENC performance (behaviour change) from baseline to one year after randomisation. We expect a larger increase in the score of determinants of EENC performance in the intervention group than in the control group. The difference between the two groups will be examined based on an intention to treat (ITT) principle with the full analysis set. The imputation of missing data will be performed using the last observation carried forward method (ITT/LOCF) and a multiple imputation method (ITT/MI) using chained equations under the assumption of missing at random.

We will use a linear random-effects mixed model employing the maximum likelihood method. We will perform a crude analysis and then adjust the results with baseline variables and other multiple variables. The same method will be used for analysing secondary outcomes such as changes in scores for skills and knowledge of EENC. Changes in the average score of the written and simulation tests between baseline and one year after randomisation will be compared between the intervention and control groups.

Sensitivity analyses will be planned using the per protocol set (PPS). A significance level of 5% with two tailed testing will be applied for all significance analyses. We will also perform subgroup analyses to assess whether the effect of self-managed continuous monitoring on EENC quality varies amongst the five main components of EENC (clean birth process, provision of warmth, support for early initiation and exclusiveness of breastfeeding, hygiene cord care and basic neonatal resuscitation).

All statistical analyses will be performed using SAS version 9.4 for Windows (SAS Institute, Cary, NC, USA).

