## Methods/design

### Trial design

This study is a cluster randomized controlled trial with four strata based on province and history of attendance for EENC coaching. It aims to evaluate superiority of self-managed continuous monitoring over supervision. It is a two-armed parallel group study. Allocation ratio is 1:1 within the same stratum.

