### Sample size and power calculation

The number of clusters, or district hospitals, is 15. We will recruit 15 health workers from each of the 15 district hospitals, 225 in total. This study is designed to detect at least a 5-point increase in the score for determinants of EENC performance (behaviour change) in the intervention group compared to the control group with 80% statistical power at a significance level of 0.05 using a 2-tailed test. There has been no previous cluster randomized studies carried out in Lao PDR. Therefore, we assume that the intra-cluster correlation coefficient (ICC) is 0.06 and that the effect size is 0.6 by referring to previous cluster RCTs in developing countries [26]. We examined the statistical power of this cluster size with this ICC and effect size. In previous studies that used the questionnaire of Planned Theory Behaviour, the largest variance in the score was 6.86 [27]. Given that variance, we expect to detect a difference of 4.1 points in the score for determinants of EENC performance with an effect size of 0.6, which is smaller than the 5-point difference we expect to detect**.** We, therefore, believe that this sample size is large enough to test the primary outcome.

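### Full maximum likelihood with only 15 hospitals understates the standard error of the arm effect by about 8% to 17% at the planned ICC, so the nominal 5% tests can run above 5%

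*Protocol article*

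**What the plan says.** For the primary endpoint, the change in the determinants score from baseline to one year, the Data analysis section says: "We will use a linear random-effects mixed model employing the maximum likelihood method". A crude fit is followed by an adjusted one, and the secondary outcomes are to be analysed in the same way. On the level of the tests it says: "A significance level of 5% with two tailed testing will be applied for all significance analyses".

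The Sample size section gives the dimensions: "We will recruit 15 health workers from each of the 15 district hospitals, 225 in total". It adds that "we assume that the intra-cluster correlation coefficient (ICC) is 0.06 and that the effect size is 0.6", and plans the trial "with 80% statistical power at a significance level of 0.05 using a 2-tailed test". Under Trial design, "Allocation ratio is 1:1 within the same stratum", with strata formed by province and history of coaching.

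The article does not say that the random effect is the hospital, which degrees of freedom or reference distribution the tests use, or whether hospital-level terms such as the strata enter the adjusted model. The Study setting section says that no stratified analyses will be done.

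**The concern.** Because whole hospitals are allocated, the precision of the arm comparison depends on the variation between 15 hospitals, not between 225 workers. Full maximum likelihood divides the between-hospital sum of squares by 15. REML divides it by 15 minus the number of hospital-level fixed effects. With hundreds of clusters the difference is negligible. With 15 it is not, and it grows with every hospital-level term added.

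An understated standard error makes confidence intervals too narrow and p-values too small. In a superiority trial whose authors expect it to influence policy in other provinces, that raises the chance of declaring the intervention better when it is not. The estimator is a stated choice, not a detail left open, so it can be assessed as written.

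**Working it through.** **Inputs.** There are 15 hospitals of 15 workers, with ICC 0.06, effect 0.6 SD and two-sided 5% (Sample size section). Xiengkhuang has 6 hospitals and Huaphanh 9 (Allocation section), with 2 previously coached in each (Study setting). The strata therefore hold 2, 4, 2 and 7 hospitals, and a 1:1 split gives 7 against 8. Assumed: a hospital random intercept, equal cluster sizes, a normal outcome, and an ICC of 0.06 for the change score.

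**The plan's own power figure.** Design effect = 1 + 14 × 0.06 = 1.84. In SD units, the true SE of the arm difference is √[(1.84/15) × (1/7 + 1/8)] = √0.03286 = 0.181, and 0.6/0.181 = 3.31.
- Power with a normal reference: Φ(3.31 − 1.96) = Φ(1.35) = 91%.
- Power with a noncentral t on 13 df: 86%.

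The stated 80% is not reproduced. The design exceeds it, so 80% serves only as a floor.

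**Size of the bias, closed form.** With p hospital-level fixed effects (intercept included), the ratio of ML to REML standard errors is √[(15 − p)/15] when the estimated hospital variance is above zero.
- Arm only, p = 2: √(13/15) = 0.931. Rejection rate against 1.96: P(|t13| > 1.96 × 0.931) = 9.1%.
- Arm plus four strata, p = 5: √(10/15) = 0.816. Rejection rate: P(|t10| > 1.96 × 0.816) = 14.1%.

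These rates overstate the problem somewhat. At ICC 0.06 the hospital variance is sometimes estimated as zero, which raises the standard error.

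**Simulation under no effect, with truncation at zero** (ICC 0.06, no stratum effect; 200,000 to 400,000 trials per setting; runs differ by 0.1 to 0.2 points):

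| Fixed effects | Mean ML SE / true SE | ML, z | ML, t on 210 df | ML, t on between-hospital df | REML, t on between-hospital df |
|---|---|---|---|---|---|
| Arm only | 0.92 | 8.3% | 8.2% | 5.8% | 4.6% |
| Arm, province, coaching history | 0.86 | 10.4% | 10.1% | 6.9% | 4.3% |
| Arm, four strata | 0.83 | 11.5% | 11.3% | 7.6% | 4.4% |

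Here 210 = 225 − 15 is the residual df, and the between-hospital df are 15 − p (13, 11 and 10). A likelihood-ratio test under ML gives 6.8% to 10.1%. REML with a normal reference gives 6.7% (arm only) and 7.2% (four strata).

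**Dependence on the ICC** (ML with z, arm only to four strata):
- 0.01: 5.7% to 6.5%
- 0.03: 7.2% to 9.0%
- 0.10: 8.9% to 13.0%
- 0.20: 9.0% to 13.9%

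**Dependence on a province difference left out of the crude model** (ML, residual ICC 0.06). The documents give no size for such a difference, so this is a range of assumptions:

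| Province difference in change score | z | t on 13 df |
|---|---|---|
| None | 8.4% | 5.9% |
| 0.2 SD | 7.4% | 5.1% |
| 0.3 SD | 6.4% | 4.3% |
| 0.4 SD | 5.1% | 3.4% |
| 0.5 SD | 3.9% | 2.5% |

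**The case against.** A reader might infer that maximum likelihood by itself takes the primary test to 8% to 12% and roughly doubles the false-positive rate. The documents do not support that, for four reasons.

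1. The 8% to 12% range also needs a normal or residual-df reference. The article names none, and a separate analysis plan may settle it. For the crude model, moving from ML with z (8.3%) to REML with z (6.7%) removes 1.6 of the 3.3 excess points; the other 1.7 come from the reference.
2. The upper end needs hospital-level covariates. Those that the article names are mostly characteristics of individual workers, and it rules out stratified analyses. Its open-ended reference to further variables makes strata terms possible, not planned.
3. The Study setting section describes real differences between the provinces. If these carry over to the change score and strata are left out, the crude model's standard error is inflated, which offsets the ML bias and can reverse it.
4. The ICC of 0.06 is borrowed from other trials. At 0.01 the inflation is about one point with z, and with between-hospital df the test is below 5%.

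All four limit the size of the claim and stand. They do not remove it. At the planned ICC and without a stratum effect, every ML-based test tried exceeds 5%, including the one with favourable degrees of freedom. A better df rule in an unseen plan would leave the level at 5.8% to 7.6% as long as ML stays. The offset from omitted strata is no safeguard, because its size is unknown and it disappears once strata enter the model, where the ML bias is largest.

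**Conclusion.** The concern holds in a limited form. As written, the estimator understates the standard error of the arm effect by about 8% (arm only) to 17% (arm plus four strata) at the planned ICC. The 5% test then runs at about 6% to 8% with between-hospital df. It reaches about 8% to 12% only with a large-sample reference, and the top of that range also needs hospital-level strata terms. A doubled false-positive rate belongs to that last combination, which the article does not commit to.

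The figures rest on a hospital random intercept, equal cluster sizes, a normal outcome, an ICC of 0.06 for the change score and, for the crude model, no stratum effect. This is a fault in a stated method that should be fixed before analysis; it is not a flaw in the design.

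**What to change.** In the Data analysis section, replace maximum likelihood by REML, with a hospital random intercept and Kenward-Roger (or between-hospital) degrees of freedom, for the primary endpoint and the secondary endpoints analysed by the same model. In SAS this is PROC MIXED with METHOD=REML and DDFM=KR. Both parts are needed: REML with a normal reference still gives about 7%, whereas REML with between-hospital df gives 4.3% to 4.6% at ICC 0.06. Quote the planned power on the same basis.

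The cost is one sentence and one line of code. Intervals become slightly wider, and power at 0.6 SD is about 86% (t, 13 df) instead of 91% (normal reference), which still exceeds the stated 80%.
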